### Participants, recruitment methods and procedures

Patients with a possible clinical indication for PPV identified by any ophthalmologist in the reference area are referred to be evaluated by the vitreoretinal surgeons of the Ophthalmology Department in the Complejo Hospitalario de Navarra, who will confirm the surgical indication, in addition to assessing the medical status and checking the current treatments in each case. The surgeon in charge will invite all subjects receiving oral anticoagulant therapy with a clinical indication for PPV to participate in the study. The purposes, methods, objectives and possible risks associated with the study will be suitably explained to them. A patient information sheet and an informed consent form will be subsequently provided. A specific consent form for the surgery will also be provided to participants. The schedule of enrolment, interventions and assessments is summarized in Figs. 1 and 2. A screening visit will be scheduled for patients who decide to participate in the study. In that visit, the inclusion and exclusion criteria will be assessed (Table 1), and patients will be informed of the group to which they will be assigned, together with the date of their operation. A description of the surgical procedure will also be provided during the screening visit. They will also be scheduled to attend an anaesthesia consultation. If the anaesthetist considers that there is a circumstance that contraindicates the interruption of anticoagulant treatment, the patient will be excluded from the trial. After PPV, they will be followed up in order to assess complications, adverse effects and visual acuity for 3 months.

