### Study randomisation

Upon completion of the screening assessment, participants who satisfy all the inclusion criteria and none of the exclusion criteria will be randomly assigned to the intervention and control groups in a 1:1 allocation ratio. Randomisation will be stratified by oral anticoagulation type: direct anticoagulation, which includes dabigatran, rivaroxaban, apixaban or edoxaban, and indirect anticoagulation, which includes acenocumarol. Randomisation assignment will be computer generated using the ‘randomizr’ library of the R statistical program R 3.4.0, with a complete randomising method based on permutations that guarantees balanced groups. The allocation sequence will be generated by the Methodology Unit of Navarrabiomed. Randomisation will be requested to the Clinical Trials Platform (CTP) of Navarrabiomed by the investigator responsible for patient recruitment. In return, CTP will send to this investigator an answer form by email that includes a randomisation number and the assigned treatment for this patient. Then, the investigator responsible for patient recruitment will give the information about treatment allocation to the anaesthetist, who will inform the patient. Throughout the study, the randomisation will be conducted by the CTP and the randomisation list will be kept by the CTP team for the duration of the study. Randomisation will be conducted without any influence of the investigators. The surgeons in charge, who will measure the outcomes, will be blinded. The data analyst will also be blinded, whereas participants and the rest of the investigators will not be blinded. Unblinding will not be allowed under any circumstance.

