### Pars plana vitrectomy

Patients will undergo PPV with the 23- or 25-gauge technique and under retrobulbar anaesthesia. PPV may be associated with facoemulsification or scleral buckling if there is a clinical indication. Blood pressure will be measured before retrobulbar anaesthesia in all patients. Before surgery, the anaesthetist in charge will verify that the patient has performed the anticoagulant procedure to which he or she was assigned. The International Normalised Ratio will be measured in those patients under treatment with acenocumarol. Retrobulbar anaesthesia will be performed according to the common technique of injecting bupivacaine 0.5% or a mixture of bupivacaine 0.5% and lidocaine 2% with a 25-gauge retrobulbar needle. Epinephrine will not be used. The volume of anaesthetic injected will be 7 ml and the injection may be repeated whenever the surgeon considers it necessary. Apart from retrobulbar anaesthesia, parenteral anxiolytics and analgesics may be administered before or during surgery. Concomitant care or interventions other than usual clinical practice are not expected.

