#### Trial governance

The Steering Committee will consist of the Principal Investigator and his research collaborators, which includes clinicians with expertise in ophthalmology. They will be responsible for the recruitment, data collection and completion of case report forms. They will also perform assessments to guarantee adherence to the study protocol. Trial management and data verification will be carried out from the centre’s CTP of Navarrabiomed and data analysis will be conducted by the Unit of Methodology of Navarrabiomed.

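### The declared blinding of the outcome assessors conflicts with the stated roles and is not protected by them

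*Protocol article*

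**What the plan says.** All places are in the protocol article.

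- **Recruitment** (Participants, recruitment methods and procedures): "The surgeon in charge will invite all subjects receiving oral anticoagulant therapy with a clinical indication for PPV to participate in the study". The same section has patients told their group at the screening visit and lists the anaesthesia consultation as a further appointment.
- **Request for allocation** (Study randomisation): "Randomisation will be requested to the Clinical Trials Platform (CTP) of Navarrabiomed by the investigator responsible for patient recruitment".
- **Receipt of allocation** (same section): "CTP will send to this investigator an answer form by email that includes a randomisation number and the assigned treatment for this patient".
- **Onward route** (same section): "the investigator responsible for patient recruitment will give the information about treatment allocation to the anaesthetist, who will inform the patient".
- **Blinding** (same section): "The surgeons in charge, who will measure the outcomes, will be blinded", while "participants and the rest of the investigators will not be blinded".
- **Trial governance**, on the Steering Committee, which includes clinicians with ophthalmology expertise: "They will be responsible for the recruitment, data collection and completion of case report forms".

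The primary endpoint (Primary and secondary endpoints) is any of a list of haemorrhagic complications before, during or up to two weeks after surgery. The list includes incoercible bleeding during surgery and postoperative anterior chamber, vitreous and intraretinal haemorrhage, with no severity threshold given.

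**The concern.** The same title, surgeon in charge, is used for the person who invites patients and for the blinded assessor. The arm is e-mailed to whoever is responsible for recruitment. On a plain reading these are the same role, so the blinded assessor may receive the allocation.

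Assessor blinding is the main protection for this endpoint, because patients and the other investigators know the arm. Whether intraoperative bleeding counts as incoercible, or a small postoperative vitreous or intraretinal haemorrhage counts as an event, is partly a matter of judgement. The question is one of non-inferiority, so if an assessor who knows the arm calls fewer events under continued anticoagulation, the bias favours a conclusion of no excess harm.

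**Working it through.** **1. The roles side by side**

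| Step | Who, as written | Section |
|---|---|---|
| Invites patients | Surgeon in charge | Participants, recruitment methods and procedures |
| Requests randomisation | Investigator responsible for recruitment | Study randomisation |
| Receives assigned treatment by e-mail | The same investigator | Study randomisation |
| Passes it on | The same investigator, to the anaesthetist | Study randomisation |
| Measures outcomes, blinded | Surgeons in charge | Study randomisation |
| Recruits, collects data, completes forms | Steering Committee as a body | Trial governance |

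Nothing separates the first row from the second, or the third from the fifth. The statements are compatible only if someone other than the patient's assessing surgeon handles the randomisation, and the article does not say so.

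**2. The plan's own figure**

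Inputs from Sample size: 96% complication-free in both arms, margin 10 points, power 80%, 95% confidence. With n = (z₁₋α + z₀.₈₀)² × 2 × 0.96 × 0.04 / 0.10²:

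- one-sided α = 0.05: (1.645 + 0.842)² × 0.0768 / 0.01 = 47.5, so 48 per arm, as stated;
- one-sided α = 0.025: 60.3, so 61 per arm, which does not match.

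The sample size is therefore consistent with a one-sided 95% limit, although the article does not state the sidedness.

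**3. How much rests on one event**

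Expected events per arm: 48 × 0.04 = 1.92. One event moves a rate by 1/48 = 2.1 points. The Wald upper limit is d + z√[p₁(1−p₁)/48 + p₀(1−p₀)/48], where d = p₁ − p₀ is continuation minus interruption. The Newcombe upper limit is d + √[(u₁−p₁)² + (p₀−l₀)²], where u₁ and l₀ are Wilson limits. Upper limits in percentage points, against a margin of 10:

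| Events, continuation vs interruption | Wald one-sided 95% | Wald two-sided 95% | Newcombe one-sided 95% |
|---|---|---|---|
| 2 vs 2 | 6.7 | 8.0 | 8.2 |
| 3 vs 2 | 9.5 | 11.0 | 10.9 |
| 4 vs 2 | 12.3 | 13.8 | 13.6 |

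Starting from 2 vs 2, one additional continuation-arm event (two with one-sided Wald) turns success into failure. Leaving the same events uncalled does the reverse.

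**4. Illustration of biased calling**

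Assumptions, none of them from the documents: true rates of 14% (continuation) and 4% (interruption), so the true difference equals the margin; a fraction m of continuation-arm events goes uncalled; control events are all called. The called continuation rate is 0.14 × (1 − m), that is 14.0, 12.6, 11.2 and 9.8%. The probability that the upper limit falls below 10 points, by exact enumeration of both binomials with n = 48:

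| Interval | m = 0 | 10% | 20% | 30% |
|---|---|---|---|---|
| Newcombe, two-sided 95% | 2.0% | 3.4% | 5.6% | 9.0% |
| Newcombe, one-sided 95% | 4.7% | 7.6% | 12.0% | 18.3% |
| Wald, one-sided 95% | 7.3% | 11.4% | 17.4% | 25.5% |

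The level depends on the interval. The rise with m does not: at m = 30% the error is roughly 3.5 to 4.5 times its value at m = 0 in every row.

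**The case against.** A reader might infer that assessment in this trial simply is unblinded, or that the statements cannot all be true. The documents do not support that.

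- The section declares the assessors blinded and forbids unblinding in any circumstance. It speaks separately of a recruiting investigator, the anaesthetist, the surgeons in charge and the other investigators.
- Inviting a patient is not the same as requesting the randomisation. Several surgeons are involved, so recruiter and assessor may differ, and passing the allocation to the anaesthetist suggests that a separation was intended.
- The Steering Committee holds its tasks collectively, which does not make one person both recruiter and assessor.

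All of this stands, and it limits the point to a blinding claim that the described roles conflict with and do not secure. It does not remove the point. This is not a detail left to a fuller document: the article itself gives both the allocation route and the blinding claim.

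Three further objections also stand in part.

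- It is tempting to argue that the preoperative INR in the acenocoumarol stratum reveals the arm. The text says only "The International Normalised Ratio will be measured in those patients under treatment with acenocumarol" and does not give the result to the assessor, so this is conjecture and no change is asked for on it.
- Choroidal and retrobulbar or peribulbar haemorrhage leave less room for judgement than the other components.
- Under-calling is only one direction. The Discussion notes that vitreoretinal surgery has been regarded as high risk for bleeding, so an assessor who knows the arm might over-call under continuation and bias the result against non-inferiority.

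**Conclusion.** The concern holds in limited form. Followed as written, the allocation route can reach the surgeon who judges the primary endpoint, and nothing in the article prevents it. Whether this happens for any given patient cannot be told from the text.

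The firm part of the size is the fragility: about 2 expected events per arm at the planned 4% rate, and a verdict that one or two classifications can reverse. The inflation of false non-inferiority is illustrative only. It rests on assumed under-calling in one arm and one direction, applied to every type of event, and on an interval method and sidedness that the article does not state.

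**What to change.** 1. In Study randomisation, have the Clinical Trials Platform send the assigned treatment directly to the anaesthetist, who already receives it and already verifies before surgery that the assigned procedure was followed. The recruiting surgeon receives only the randomisation number.
2. Reconcile Participants, recruitment methods and procedures with Study randomisation, so that the anaesthetist tells the patient the group and it is not announced by the surgeon at the screening visit. Ask patients not to mention their regimen at eye examinations.
3. State, in line with Trial governance, that whoever knows a patient's allocation does not assess that patient's primary endpoint.
4. Recruitment began on 1 April 2019 (Trial status), and an amendment cannot restore blinding for patients already assessed. For those already enrolled, report who knew the allocation.

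The cost is a minor protocol amendment: a different e-mail recipient and a few sentences. It needs no additional patients or staff.

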### Study arms

In the control group (representing the standard of care), anticoagulant therapy will be interrupted before surgery and patients will receive substitutive treatment with subcutaneous enoxaparin in accordance with the currently employed protocol in the hospital.

To establish substitution therapy, the thrombotic risk of patients is evaluated, taking into account their clinical characteristics. Their renal function is also evaluated by measuring the glomerular filtration rate. In patients undergoing treatment with acenocumarol, if the thrombotic risk is low, they will be treated with enoxaparin 40 mg/24 h; if the thrombotic risk is high and the glomerular filtration rate is less than 30 ml/min, they will be treated with enoxaparin 40 mg/24 h; if the thrombotic risk is high and the glomerular filtration rate is greater than 30 ml/min, they will be treated with enoxaparin 40 mg/12 h. In patients undergoing treatment with the new direct action oral anticoagulants, if the glomerular filtration rate is less than 50 ml/min or if the thrombotic risk is high, the treatment is replaced 5 days before with enoxaparin 40 mg/24 h. If the glomerular filtration rate is greater than 50 ml/min and the thrombotic risk is low, anticoagulant treatment is suspended without the need for substitution treatment.

For the intervention group oral anticoagulant therapy will not be interrupted. Patients will continue their regular oral anticoagulant therapy before and after surgery.

### Pars plana vitrectomy

Patients will undergo PPV with the 23- or 25-gauge technique and under retrobulbar anaesthesia. PPV may be associated with facoemulsification or scleral buckling if there is a clinical indication. Blood pressure will be measured before retrobulbar anaesthesia in all patients. Before surgery, the anaesthetist in charge will verify that the patient has performed the anticoagulant procedure to which he or she was assigned. The International Normalised Ratio will be measured in those patients under treatment with acenocumarol. Retrobulbar anaesthesia will be performed according to the common technique of injecting bupivacaine 0.5% or a mixture of bupivacaine 0.5% and lidocaine 2% with a 25-gauge retrobulbar needle. Epinephrine will not be used. The volume of anaesthetic injected will be 7 ml and the injection may be repeated whenever the surgeon considers it necessary. Apart from retrobulbar anaesthesia, parenteral anxiolytics and analgesics may be administered before or during surgery. Concomitant care or interventions other than usual clinical practice are not expected.

### Primary and secondary endpoints

The primary endpoint is the presence of any of the following complications: 1) retrobulbar or peribulbar haemorrhage after local anaesthesia (preoperative complication); 2) choroidal haemorrhage or incoercible haemorrhage in the anterior chamber or vitreous cavity during surgery (intraoperative complications); and 3) during the first 2 weeks after surgery, anterior chamber haemorrhage, vitreous haemorrhage, intraretinal haemorrhage or choroidal haemorrhage (postoperative complications). These haemorrhagic complications can be divided according to their clinical relevance into major (choroidal haemorrhage and retrobulbar or peribulbar haemorrhage) and minor (anterior chamber haemorrhage, vitreous haemorrhage and intraretinal haemorrhage). The secondary endpoints are: 1) a change in the corrected visual acuity after surgery (measured as the difference between baseline and 3 months after surgery, in the decimal scale and converted into logMAR scale); 2) thromboembolic events during the first 3 months after surgery; and 3) other surgical procedure-related complications during the first 3 months after surgery.

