### Secondary objectives

Our secondary objectives are to compare changes in the visual results 3 months after PPV in patients who maintain anticoagulant therapy compared to those with interruption of this therapy before surgery and to compare the incidence of systemic thromboembolic events after PPV in those patients who maintain anticoagulant therapy compared to those with interruption of this therapy before surgery.

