### Hypothesis

We hypothesise that anticoagulant therapy maintenance before PPV is not associated with a significant increase in perioperative complications compared to those cases in which this therapy is interrupted before surgery, and that the postoperative visual results are not inferior in those cases in which anticoagulant therapy is maintained compared to those cases in which such therapy is interrupted before surgery.

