### Statistics

#### Sample size

Considering that there is no difference in the probability of not having complications between the standard therapy (anticoagulant interruption) and the experimental therapy (no interruption of anticoagulant), and assuming a 95% confidence level and a 96% probability of not having complications, 48 patients are required in each arm (*n* = 48 × 2) in order to have an 80% probability that the upper limit of the confidence interval excludes a difference of over 10% in favour of the standard group. Calculations are performed by Sealed Envelope Ltd.

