#### Data analysis

A description of the sociodemographic and clinical characteristics of the patients involved in this trial will be performed for the complete sample and for each group using a mean with standard deviation or median with interquartile range for the quantitative variables, and using frequencies and percentages for the categorical variables. These characteristics will be compared between the control and experimental groups using parametric tests such as the Student *t* test and Chi-squared test, or nonparametric tests such as the Mann–Witney or Fisher tests. If any of the variables differs significantly between groups, this will be taken into account when comparing the outcomes. The incidence of haemorrhage (pre-, intra- and postoperative) and other categorical secondary variables, such as complications 3 months after surgery, both for the total sample and for each group, will be estimated by means of sample proportion with a 95% confidence interval and from baseline to 3 months after surgery will be compared between groups using parametric or nonparametric tests, such as the Student *t* test and Mann–Whitney test, depending on normality. If any sociodemographic or clinical characteristic differs between groups, lineal and logistic regression models will be used to compare the outcomes between groups, including them as covariates, which will provide adjusted odds ratios for the intervention, together with 95% confidence intervals. Sensitivity analyses will also be performed excluding patients with proliferative vitreoretinopathy or proliferative diabetic retinopathy, patients for whom scleral buckling procedures have been placed, and patients under treatment with acetylsalicylic acid to account for the possible bias induced after having included them. Additionally, a multivariate analysis including age and treatment with acetylsalicylic acid will also be performed to account for possible differences in the distribution of these variables among groups. SPSS software version 21.0 will be used to perform the analysis.

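### Visual acuity is hypothesised to be non-inferior with no acuity margin and an ordinary difference test, baseline acuity is not a fixed covariate, and the logMAR conversion is worded ambiguously

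*Protocol article*

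**What the plan says.** Four parts of the protocol article bear on visual acuity.

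- **Hypothesis.** The second limb is that "the postoperative visual results are not inferior in those cases in which anticoagulant therapy is maintained".
- **Secondary objectives.** The aim is only to "compare changes in the visual results 3 months after PPV"; non-inferiority is not mentioned.
- **Primary and secondary endpoints.** The first secondary endpoint is change in corrected acuity, "measured as the difference between baseline and 3 months after surgery, in the decimal scale and converted into logMAR scale".
- **Data analysis.** Baseline-to-3-month outcomes are to be "compared between groups using parametric or nonparametric tests, such as the Student *t* test and Mann–Whitney test, depending on normality". If a characteristic differs between groups, "lineal and logistic regression models will be used to compare the outcomes between groups, including them as covariates". In addition, "a multivariate analysis including age and treatment with acetylsalicylic acid will also be performed". The confidence intervals this section mentions are for proportions and for odds ratios.

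The only margin in the document is in Sample size, where the design aims that "the upper limit of the confidence interval excludes a difference of over 10% in favour of the standard group". It refers to complications. Randomisation is stratified by type of oral anticoagulant, direct or indirect (Study randomisation).

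**The concern.** There are three linked weaknesses.

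1. **Hypothesis and test do not match.** Non-inferiority is judged by setting a confidence interval against a margin. A t or Mann–Whitney test asks whether the arms differ, and in a trial of this size it can miss a sizeable loss of vision. The Hypothesis section words its complications limb as the absence of a significant increase, so a reader could easily take non-significance as support for the acuity limb too.
2. **Baseline acuity and the stratum are not fixed covariates.** Baseline acuity has to be measured for the endpoint to exist, yet whether it enters a model depends on whether the arms happen to differ. That gives up precision and leaves the model to be chosen after the data are seen.
3. **The endpoint definition can be read two ways.** Under one reading each acuity is converted and then subtracted. Under the other the decimal difference is converted, which is not a logMAR change at all.

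The interpretation of one limb of the stated hypothesis is at stake. The primary endpoint is not affected.

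**Working it through.** **The plan's own figure.** Inputs from Sample size: 96% free of complications in both arms, margin 10%, 95% confidence, 80% power.

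n per arm = (1.645 + 0.842)² × 2 × 0.96 × 0.04 / 0.10² = 6.18 × 7.68 = 47.5, so 48.

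This reproduces the stated 48, with a one-sided 5% level (one-sided 2.5% would give 61). The calculation concerns complications only. The document gives no margin, SD or power for acuity, so the acuity figures below rest on assumed values.

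**What a non-significant acuity test could hide.** Assume an SD of logMAR change of 0.3, 0.5 or 0.7, with 48 per arm. The 95% half-width is 1.986 × SD × √(2/48), with √(2/48) = 0.204. If the observed difference is just short of significance, it nearly equals the half-width, so the unfavourable limit is about twice that.

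| Assumed SD of change | Half-width | Unfavourable limit, just non-significant | Smallest margin shown with 80% power, one-sided 5% | Same, one-sided 2.5% |
|---|---|---|---|---|
| 0.3 | 0.12 | 0.24 | 0.15 | 0.17 |
| 0.5 | 0.20 | 0.41 | 0.25 | 0.29 |
| 0.7 | 0.28 | 0.57 | 0.36 | 0.40 |

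The last two columns assume no true difference and use (1.645 + 0.842) × SD × 0.204 and (1.960 + 0.842) × SD × 0.204.

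**Precision.** Let r be the correlation between baseline and 3-month logMAR, and take equal SDs at both visits, scaled to 1.

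- Variance of the change score: 2(1 − r).
- ANCOVA residual variance: 1 − r².
- Ratio: (1 − r²) / [2(1 − r)] = (1 + r)/2.

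| Assumed r | Variance ratio | Interval narrower by (1 − √ratio) | Patients giving the precision of 96 |
|---|---|---|---|
| 0.3 | 0.65 | 19% | 62 |
| 0.5 | 0.75 | 13% | 72 |
| 0.7 | 0.85 | 8% | 82 |

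If the SDs differ, with k the baseline SD divided by the 3-month SD, the change-score variance exceeds the ANCOVA variance by (1 + k² − 2rk) − (1 − r²) = (k − r)². This is never negative, so the direction of the gain does not depend on equal SDs. Its size does, and it vanishes if k = r. These ratios concern baseline acuity only; no gain is counted for the stratum.

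**Order of conversion.** logMAR = −log10(decimal acuity).

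| Decimal acuity, baseline to 3 months | Decimal difference | logMAR change (negative = gain) | −log10 of the difference |
|---|---|---|---|
| 0.1 to 0.5 | 0.4 | −0.699 | 0.398 |
| 0.5 to 0.9 | 0.4 | −0.255 | 0.398 |
| 0.5 to 0.5 | 0 | 0 | undefined |
| 0.5 to 0.4 | −0.1 | 0.097 | undefined |

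Converting the difference gives the same value to two very different gains and no value to eyes that stay the same or worsen.

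**The case against.** **On the conversion.** A reader might infer that decimal differences will be converted. The text does not show this. The closing words of the definition can equally describe units: acuity recorded in decimal and expressed in logMAR for the change. Because the literal reading is undefined for any eye that does not improve, it is unlikely to be intended. This objection stands: the fault is one of clarity, and the table above shows only what the wrong reading would do.

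**On adjustment.** A reader might infer that acuity is compared only by unadjusted tests. That is not so. Data analysis provides for regression when characteristics differ, and for an unconditional model with age and acetylsalicylic acid. What remains is that adjustment for baseline acuity is conditional on what the baseline comparison shows, and that neither it nor the stratum is named in the unconditional model.

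**On the test.** The sentence naming the t and Mann–Whitney tests has no clear subject as it reads in the available text, and acuity is not named in it. Applying it to acuity is an inference, though a strong one, because acuity change is the endpoint defined as a baseline-to-3-month difference.

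**On validity.** Under randomisation a comparison of change scores is valid. The case for ANCOVA is efficiency, and its size rests on an assumed correlation.

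**On the missing margin.** Acuity is a secondary endpoint, the objective speaks only of comparing changes, and an analysis plan not shown may give a margin and covariates. Nothing says that a non-significant test will be reported as non-inferiority. All of that is fair. But the article itself states a non-inferiority hypothesis and appears to name a difference test for it, and as published those two do not fit together.

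**Conclusion.** The point holds in a limited form. The firmest part is the mismatch: a non-inferiority hypothesis for acuity, no acuity margin in the document, and an apparent difference test that cannot support it. For assumed SDs of change of 0.3 to 0.7 logMAR, a just non-significant result could coexist with a disadvantage of about 0.24 to 0.57 logMAR.

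The second part is an avoidable loss of precision. ANCOVA on baseline acuity would have 0.65 to 0.85 of the change-score variance for an assumed correlation of 0.3 to 0.7 with equal SDs. That is worth having in a trial that lists its small number of patients among its limitations, but it does not make the planned comparison wrong.

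The third part is an endpoint definition that should not admit an invalid reading. The documents do not support saying that the acuity analysis is invalid, that it is wholly unadjusted, or that a false non-inferiority claim is planned. The matter should be corrected, at the level of a secondary endpoint.

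**What to change.** 1. In Primary and secondary endpoints, state that each reading is converted to logMAR before any subtraction.
2. In Data analysis, name visual acuity explicitly. Analyse 3-month logMAR by ANCOVA with baseline logMAR and anticoagulant stratum as prespecified covariates, whatever the baseline comparison shows, and report the adjusted mean difference with its 95% confidence interval.
3. Then choose one of two courses. Either state a justified logMAR non-inferiority margin before any outcome data are seen by arm, and judge the interval against it; or remove the non-inferiority wording for acuity from the Hypothesis and present the interval as estimation, which would match the Secondary objectives as they stand.

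The cost is wording and slightly more analysis work. No new data are needed, because baseline acuity is already part of the endpoint. The trial may have to make a more modest claim about vision: with 48 per arm, the table of margins shows that a tight margin may be out of reach if the SD is large.
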